## **Purpose**

The aim of this study was to compare the time-course of post-exercise parasympathetic reactivation of the heart and changes in local and regional indices of arterial stiffness to different fitness classes (Bike, Pump Power and Global Training), as prescribed for health [34] and commercially available.

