**FIGURE 1: TIMELINE AND MAIN OUTCOME VARIABLES OF PUMPING ARTERIES**

\* INTERVENTIONS WILL BE RANDOMIZED. THE TIMELINE HEREIN DISPLAYED IS MERELY A GRAPHIC REPRESENTATION OF A PARTICIPANT'S ACTIVITIES FOLLOWING RANDOMIZATION.

In each session, participants will initially undertake 20-min of supine rest on a cushioned examination table with resting energy expenditure measured by indirect calorimetry (K5, Cosmed, Rome, Italy) and heart rate and blood pressure recorded continuously using digital plethysmography technique (Finapres® Nova, Ohmeda, 2 Louisville, Colorado, USA), followed by regional assessments of PWV and pulse wave analysis of the aortic, brachial and femoral arteries on the right side of the body using applanation tonometry (Colson Analyze, ALAM Medical, Paris, France), and carotid arterial stiffness indices and wave intensity analysis using an ultrasound (Arietta V60, Hitachi Aloka Medical Ltd, Mitaka-shi, Tokyo, Japan). In the time following, participants will perform one of three exercise sessions (Bike, Pump Power or Global Training). Exercise sessions will consist of either a 45-minute class of Bike, Pump Power, and Global Training, while energy expenditure will be continuously measured by indirect calorimetry (K5, Cosmed, Rome, Italy) (Figure 2). These sessions are characterized by distinct metabolic demands, representing the typical sessions provided by gyms and health clubs to improve or maintain cardiovascular health. In the control condition, the participants will remain quietly seated for 45-min, maintaining a good posture. Only one participant will be tested per class with approximately 10-20 non-research participants also performing each group fitness class alongside the research participants. Upon completion of each intervention/session, participants will return immediately to the examination table and recover in the supine position for 30-min while hemodynamic and stiffness indices are reevaluated at 10, 20- and 30-min following recovery and compared to those at rest.

|                       | Rest |    | Exercise Session | Recovery |    |    |
|-----------------------|------|----|------------------|----------|----|----|
|                       | 15   | 20 | 45               | 10       | 20 | 30 |
| Advanced Hemodynamics |      |    |                  |          |    |    |
| Arterial Stiffness    |      |    |                  |          |    |    |

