### **Statistical Analysis and Data Monitorization**

Based upon a medium effect size of 0.154 derived from published changes in aortic PWV within-between modes of exercise [18], an a priori power analysis suggested that 22 participants are required to detect significant differences within-between groups, conditions and time points ( $1-\beta = 80\%$ ,  $\alpha = 0.05$ ). All data will be collated and/or analyzed using Microsoft Excel (v15.29.1, Microsoft Corporation, Redmond, Washington, United States) and Statistical Package for the Social Sciences version 24 (IBM, Armonk, New York, United States) software with results presented as mean  $\pm$  SD. Due to technical issues, missing data (~4–5%) may be evident during the study and subsequently should be replaced by averaging values before and after the missing value for the relevant variable prior to analysis.

Comparisons between interventions (Bike, Pump Power, Global Training and Control) over time (Rest vs. post-intervention time points) for indices of autonomic and vascular function will be examined via two-way

(intervention × time), repeated measures analysis of variance (ANOVA) and adjusted for sex and activity energy expenditure. Session differences for indices of autonomic and vascular function and energy expenditure will be analyzed using a one-way repeated measures ANOVA. Post-hoc comparisons will be conducted via Bonferroni's tests. Statistical significance will be set at  $p < 0.05$ .

The database will be stored in the GCP private server throughout the study period. The GCP lab will be responsible for management, storage and is the single user of the complete database.

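### The intervention × time comparison is adjusted for activity energy expenditure, which the assigned class itself produces, so it does not estimate the stated comparison of the classes as delivered

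*Protocol*

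**What the plan says.** Under Statistical Analysis and Data Monitorization, autonomic and vascular indices are compared between the four conditions over time by a two-way (intervention × time) "repeated measures analysis of variance (ANOVA) and adjusted for sex and activity energy expenditure". No version of this intervention × time analysis without the adjustment is given.

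The following sentence reads: "Session differences for indices of autonomic and vascular function and energy expenditure will be analyzed using a one-way repeated measures ANOVA". Energy expenditure is therefore both a covariate and a session outcome. This second analysis names no covariates and no time point.

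The session description under Figure 1 (Design) says of the 45-minute classes, "while energy expenditure will be continuously measured by indirect calorimetry (K5, Cosmed, Rome, Italy". It goes on: "These sessions are characterized by distinct metabolic demands". For the comparator: "In the control condition, the participants will remain quietly seated for 45-min".

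The Purpose section sets out to compare recovery of parasympathetic activity and changes in arterial stiffness after the three classes, "as prescribed for health [34] and commercially available". No aim of comparing them at equal energy cost is stated.

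**The concern.** Adjustment is safe for variables that the randomised condition cannot influence. Energy expenditure during the session comes after assignment, and by the protocol's own account it differs between classes. It is a plausible route by which a harder class changes arterial stiffness or vagal recovery more than an easier one.

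Holding it constant changes the question from how the classes differ as people take them to how they would differ if each cost the same energy. For Control, that means seated rest at an exercise-level expenditure, or a class at a resting one. Neither occurs, so that part of the comparison rests on extrapolating the covariate slope.

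Three things are at stake. A real class difference could be shrunk or erased. A difference could appear where the classes do not differ overall. And precision could be lost in a trial of 12 participants (Participants section) or 22 (power statement).

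**Working it through.** **Plan's own figure.** There is none to reproduce: the protocol gives no mean or SD for energy expenditure. All energy values below are assumptions.

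**Reading assumed.** The covariate has one value per participant per session, which is how it is measured. The calculation takes one outcome per session, such as the change from rest to a given recovery time. In the intervention × time model this means that the covariate may act on the change. If it entered only as an additive term that is constant within a session, it would cancel from rest-to-recovery changes and alter only the average level of each session. The protocol does not say which is meant.

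**1. Precision.** With n participants and four conditions, the residual degrees of freedom are 3(n − 1), which is 33 at n = 12. Adding the covariate multiplies the variance of a two-condition contrast by

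1 + d² / [(2/n) × 3(n − 1) × s²],

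where d is the difference in mean energy expenditure between the two conditions and s is its residual within-participant SD. At n = 12, (2/12) × 33 = 5.5. The residual variance of the outcome is held fixed.

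Assume Control 60 kcal, class means within 260–450 kcal, and s = 40–90 kcal.

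| Contrast | d (kcal) | s (kcal) | Calculation | Variance factor |
|---|---|---|---|---|
| Costliest class vs Control | 390 | 40 | 1 + 152,100/8,800 | 18.3 |
| Costliest class vs Control | 390 | 90 | 1 + 152,100/44,550 | 4.4 |
| Least costly class vs Control | 200 | 40 | 1 + 40,000/8,800 | 5.5 |
| Least costly class vs Control | 200 | 90 | 1 + 40,000/44,550 | 1.9 |
| Widest gap between classes | 190 | 40 | 1 + 36,100/8,800 | 5.1 |
| Widest gap between classes | 190 | 90 | 1 + 36,100/44,550 | 1.8 |
| Classes of equal cost | 0 | any | 1 + 0 | 1.0 |

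The choice between 12 and 22 participants hardly matters. At n = 22 the multiplier is (2/22) × 63 = 5.73, and the top row becomes 1 + 152,100/(5.73 × 1,600) = 17.6.

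**2. What is estimated.** A simulation used 800 replicates per setting and a different assumed scale: mean expenditure 1.2 (Control), 4 (Pump Power), 6 (Global Training) and 8 (Bike), s = 0.5 to 2.0, outcome residual SD 0.5, and a true Bike − Control effect of −0.68. Results at n = 12:

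| Scenario | Unadjusted estimate | Adjusted estimate | Power of 3-df test, unadjusted → adjusted |
|---|---|---|---|
| Effect wholly through energy expenditure | about −0.68 | about 0 | 0.74–0.79 → 0.04–0.06 |
| Half through energy expenditure | about −0.68 | −0.29 to −0.36 | 0.78–0.81 → 0.06–0.12 |
| Energy expenditure has no effect on outcome | about −0.68 | −0.62 to −0.69 | 0.79–0.80 → 0.07–0.33 |
| Direct and mediated effects cancel (total effect zero) | about 0 | +0.32 to +0.39 | not applicable |

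The Bike − Control standard error was multiplied by about 6.0 at s = 0.5 and by 1.7–1.8 at s = 2. The formula, on the standard-error scale with d = 6.8, gives 5.88 and 1.76, so the two agree. For classes 2 units apart the formula gives 1.98 to 1.09, and for classes 4 units apart 3.55 to 1.31. On this scale the largest variance factor is 5.88² = 34.6. The upper ends in step 1 are therefore not bounds; they follow from the energy spread assumed.

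**The case against.** The strongest reply is that class type at fixed energy cost is a coherent question. The introduction is motivated by exercise mode and notes that metabolic costs of group classes are undescribed. This stands as a reason to keep such an analysis, but not as the main one: the Purpose section does not ask it, and it cannot sensibly include Control.

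The loss may also be small. Between classes of similar cost the variance factor is near 1, and if energy expenditure strongly predicts the outcome, lower residual variance would offset part of the inflation. Both points stand.

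The mechanism also depends on how the covariate is entered. One value per participant would not remove within-participant class differences in this way. The protocol does not say, although measurement is by session.

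A reader might infer more than the protocol supports:

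- **That sex should go too.** Sex is a baseline characteristic that the class cannot alter. Keeping it is a matter of preference.
- **That energy expenditure is not measured in Control.** The cell marks in the Figure 1 and Figure 2 tables are not legible in the text at hand, resting expenditure is measured in each session, and a one-way analysis of energy expenditure by session is planned. Absence cannot be concluded.
- **That the model cannot be fitted in the named software.** The protocol names the package but no procedure, so this would rest on knowledge from outside it.
- **That every comparison of the vascular and autonomic indices is adjusted.** The one-way analysis covers them with no stated covariates. It is partial cover only: its time point is not given and it does not replace an unadjusted intervention × time test.
- **That type I error is generally inflated.** What is shown is a larger standard error and a different target of estimation.

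**Conclusion.** The point holds. The only stated intervention × time analysis conditions on a variable that is measured after assignment, is driven by the assigned session and is itself treated as an outcome. With a session-level covariate acting on the change from rest, it does not estimate the difference between the classes as delivered. That conclusion follows from the protocol's text and needs no numbers.

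The size is illustrative. Under the kcal assumptions, the contrast variance is multiplied by roughly 2–18 for a class versus Control and by near 1 to about 5 between classes, before any gain from lower residual variance. The share of the effect removed equals the share that runs through energy expenditure, which is unknown.

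**What to change.** In Statistical Analysis and Data Monitorization, state that the main intervention × time analysis is fitted without activity energy expenditure. Keep the planned one-way comparison of energy expenditure between sessions. If a comparison net of energy cost is wanted, label it exploratory, limit it to the three exercise classes, and say whether the covariate is entered per session and whether it is crossed with time. The adjustment for sex need not change.

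The cost is about one sentence in the analysis section. No measurement, visit or data collection changes.

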## **Methodological Procedures**

### **Participants**

Twelve apparently healthy adults aged between 21 to 34 years will be included in this study. These will be recruited from the professional network of GCP. We do not expect these adults to be enrolled in any other scientific study besides PUMPING ARTERIES. Informed written consent will be signed by volunteers prior to the first evaluation day (Figure 1) in accordance with approval by the Ethical Committee of Faculdade de Motricidade Humana – Universidade de Lisboa. We expect recruited participants to be outwardly active with some experience in both aerobic and resistance exercise (~3–4 times/week, >3 months). No trained athletes will be included in the cohort. All participants will be healthy or perceived to be healthy based on the sport's medical examination or the preparticipation screening process. Exclusion criteria include any form of cardiovascular disease, more than one cardiovascular disease risk factor, resting hypertension (systolic blood pressure >140 mmHg, diastolic blood pressure > 90 mmHg), any prescription medication use, and currently smoking.

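### A cheap improvement, not an error: Holm's step-down adjustment would find more true pairwise differences than single-step Bonferroni at the same 5% family-wise error

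*Protocol*

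**What the plan says.** The Purpose section sets out to compare parasympathetic reactivation and "changes in local and regional indices of arterial stiffness to different fitness classes (Bike, Pump Power and Global Training"). The section Statistical Analysis and Data Monitorization plans a two-way repeated-measures ANOVA for "Comparisons between interventions (Bike, Pump Power, Global Training and Control) over time", with Rest set against the post-intervention time points, and a one-way repeated-measures ANOVA for session differences. It then states "Post-hoc comparisons will be conducted via Bonferroni" and a significance level of 0.05. It does not list the comparisons that make up the Bonferroni family.

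On size, the Participants section says "Twelve apparently healthy adults aged between 21 to 34 years will be included in this study", while the statistical section says "an a priori power analysis suggested that 22 participants are required". The Design section makes the study a randomised crossover, so all pairwise comparisons of sessions are paired.

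**The concern.** An omnibus F test does not say which classes differ, so the pairwise tests carry the answer to the study question. The protocol fixes the adjustment for them as Bonferroni, which compares every p-value with 0.05/m for m comparisons, however many have already been rejected. Holm's method relaxes the threshold after each rejection and controls the family-wise error under any dependence between the tests. With few participants, true differences may be missed that the same data would show at the same error rate. This is a choice the protocol states, not a detail it leaves open.

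**Working it through.** **Inputs.** Twelve participants (Participants) or 22 (statistical section); four sessions, hence 4×3/2 = 6 pairs, or 3×2/2 = 3 pairs if only the classes are compared; α = 0.05. Assumed, because the documents do not give them: two-sided paired t tests, one outcome at one time point, equal variances, no covariate adjustment, and effects in SDs of the paired difference.

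**The plan's own figure.** The 22 is not tied to the post-hoc tests. It also cannot be reproduced uniquely, because the metric of the effect size 0.154, the correlation and the numbers of groups and measurements are not given. With one group and correlation 0.5, reading 0.154 as Cohen's f gives 59 participants for 4 measurements or 26 for 16; reading it as partial η² gives 9 or 5. Other unstated settings give 20 to 24, so 22 cannot be called wrong.

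**Thresholds for the ordered p-values.**
- Bonferroni: 0.05/m at every step.
- Holm: 0.05/(m − j + 1) at step j. For six pairs: 0.05/6, /5, /4, /3, /2, /1.
- Shaffer: for three pairs 0.05/3, then 0.05 for both others, since after one pair truly differs at most one of the other two can be equal. For six pairs: 0.05/6, /3, /3, /3, /2, /1.

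No Holm threshold is below Bonferroni's, so Holm loses no rejection. The first thresholds are the same, so whether anything at all is rejected does not depend on the choice.

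**Exact power for one pair at 0.8 SD.** The noncentrality is 0.8√n: 2.77 on 11 df for n = 12, and 3.75 on 21 df for n = 22.

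| n | α = 0.05 | 0.05/3 | 0.05/6 |
|---|---|---|---|
| 12 | 71% | 51% | 38% |
| 22 | 95% | 86% | 79% |

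**Simulated power at n = 12** (40,000 runs per pattern; power for each true difference of the stated size).

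| Pattern of means | Difference | Bonferroni | Holm | Shaffer |
|---|---|---|---|---|
| Classes 0, 0, 0.8 | 0.8 | 51% | 55% | 60% |
| Classes 0, 0.4, 0.8 | 0.4 (adjacent) | 12% | 15% | 20–21% |
| Classes 0, 0.8, 1.6 | 0.8 (adjacent) | 51% | 66–67% | 71% |
| Four sessions 0, 0, 0, 0.8 | 0.8 | 38% | 41% | 46% |
| Control 0; classes 2, 2, 2.8 | 0.8 (between classes) | 38% | 55% | 55% |
| Control 0; classes 2, 2.8, 3.6 | 0.8 (adjacent classes) | 38% | 67% | 67% |

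The large gains need one or more comparisons that are almost certain to be rejected first. In the third row the outer classes are 1.6 SD apart and are separated in 99% of runs. In the last two rows the Control pairs play that part.

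The chance of finding at least one true difference was 69% under all three methods for classes 0, 0, 0.8, and 65–66% under all three for one session apart among four. The chance of finding every true difference rose from 33% to 41% (Holm) and 52% (Shaffer) in the first case, and from 14% to 19% and 24% in the second.

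**Error rate.** The simulated family-wise error stayed below 5% for all three methods in every pattern. Under the global null it was about 4–5% and the same for all three.

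**The case against.** The strongest reply is that Bonferroni is a valid, prespecified procedure, that the protocol never claims it is the most powerful one, and that the same remark could be made of any trial using it. That stands: a reader might infer that the post-hoc plan is wrong or fails to control error, and the documents do not support that.

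It is also fair that the gain is small in plain patterns. With one session apart among four, Holm adds about 3 points, whereas going from 12 to 22 participants adds about 40 (38% to 79% at 0.8 SD over six pairs). A reader might infer that a better adjustment would cure the shortage of power. It would not.

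Two other stronger readings fail. If every session-by-time pair counted, the family could be as large as 48, and power for 0.8 SD would be 13%. Setting that against Holm on nine comparisons (47–48% with class means 0, 0.8, 1.6) mostly measures the smaller family: Bonferroni on the same nine already gives 32%. Nothing in the protocol says the family is 48. Second, the phrase "with results presented as mean" ± SD might suggest that no paired differences will be reported. It describes a summary format and excludes nothing, and such detail is commonly left to a statistical analysis plan.

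What remains against the objection is that Holm loses no rejection for the same family, can gain a good deal if Control lies far from the classes, and costs almost nothing.

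**Conclusion.** The point holds as a cheap improvement. Single-step Bonferroni is correct but gives away power that Holm recovers at the same family-wise error. At n = 12 and 0.8 SD, Holm's gain is about 3 to 4 points when one session or class differs from otherwise equal ones. It is about 16 points for classes at 0, 0.8, 1.6, and about 16 to 28 points on class differences when Control differs strongly from every class. The gain in the chance of finding any difference is essentially nil.

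These sizes rest on assumed effects and on families of three or six pairs. The protocol gives neither the effects nor the family, so the actual loss cannot be derived from it; only its direction is certain. The power figures also take n = 12, which conflicts with the 22 in the statistical section. That conflict matters more for power and needs its own correction. At n = 22 the adjustment still matters: 79% at 0.05/6 against 95% at 0.05.

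**What to change.** Replace the Bonferroni sentence by, for example: *Post-hoc tests cover the planned comparisons (all four sessions, Control included, and Rest against each recovery time). Within each family, p-values are adjusted by Holm's step-down method in place of single-step Bonferroni.*

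The family should not be cut down to the three class pairs in passing: the protocol plans comparisons with Control and with Rest, and dropping them would be a separate decision. Shaffer's thresholds are an optional further gain where a family consists of all pairs of a set of sessions.

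The cost is one sentence and perhaps a few lines in the spreadsheet already named for the analysis, since Holm needs only the unadjusted p-values. The downside is that Holm has no simple simultaneous confidence intervals, so ordinary 95% intervals shown beside the adjusted p-values may occasionally disagree with them.

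### No primary outcome is named although the sample size rests on aortic PWV, and about 18–22 indices are each tested at 0.05 with no control across indices

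*Protocol*

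**What the plan says.** The Purpose section sets a joint aim: to compare, across three fitness classes, the time-course of "post-exercise parasympathetic reactivation of the heart and changes in local and regional indices of arterial stiffness". Neither half is ranked above the other. The caption of Figure 1 speaks of main outcome variables in the plural, and the rows of that figure are assessment domains, not a chosen endpoint.

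The section Statistical Analysis and Data Monitorization sizes the study on one index: "Based upon a medium effect size of 0.154 derived from published changes in aortic PWV within-between modes of exercise", with the result that "an a priori power analysis suggested that 22 participants are required to detect significant differences within-between groups, conditions and time points" (80% power, alpha 0.05).

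The same section then fixes the tests:
- For all autonomic and vascular indices, "Comparisons between interventions (Bike, Pump Power, Global Training and Control) over time (Rest vs. post-intervention time points") are examined by two-way (intervention × time) repeated-measures ANOVA.
- The same indices, together with energy expenditure, are tested again by one-way repeated-measures ANOVA.
- The threshold is common to all: "Statistical significance will be set at" p < 0.05.
- The only multiplicity control is "Post-hoc comparisons will be conducted via Bonferroni's tests". Nothing extends it from one index to another.

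**The concern.** Aortic PWV determines the sample size but has no special standing in the analysis. Each of the other indices is tested at the same threshold and could equally be presented as the trial's answer. The Bonferroni step limits error among pairs of interventions within an index; it does nothing about choosing among indices. If aortic PWV shows nothing and another index crosses 0.05, the plan gives no reason to treat that index as anything less than the main result.

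**Working it through.** **1. The plan's own sample size.** The protocol does not say what kind of effect size 0.154 is, and gives no correlation between repeated measurements. Read as Cohen's f, for the 4 × 4 within-participant interaction (four interventions; rest, 10, 20 and 30 min) and with an assumed correlation ρ = 0.5:

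λ = f² × 16 / (1 − ρ) × N = 0.023716 × 32 × N = 0.759 × N, with df 9 and 9(N − 1).

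- N = 21: λ = 15.9, power 78.6%
- N = 22: λ = 16.7, power 81.0%

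This returns the stated 22. The match depends on the assumption: the same formula gives 43 at ρ = 0, 14 at ρ = 0.7 and 10 at ρ = 0.8. It is therefore consistent with the statement but does not prove how the calculation was done. On any reading, the only outcome behind it is aortic PWV.

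**2. Counting the indices**, by protocol section:

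| Section | Indices | Number |
|---|---|---|
| Advanced Hemodynamics | HR, SV, CO, R, C, Zc | 6 |
| Effective Arterial Elastance | Ea, ESP | 2 |
| Heart rate variability | LF, HF, LF/HF | 3 |
| Baroreflex Sensitivity | transfer gain | 1 |
| Brachial Blood Pressure | SBP, DBP | 2 |
| Aortic and Limb Arterial Stiffness | three PWVs | 3 |
| Carotid Blood Pressure | carotid SBP | 1 |
| Carotid Arterial Stiffness Indices | elastic modulus, β, AIx | 3 |
| Carotid Blood Pressure Wave Intensity | net wave intensity | 1 |
| **Total** | | **22** |

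If HR, SV, CO and ESP are not counted as autonomic or vascular, 18 remain.

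**3. One interaction test per index, no true differences, independence.** The chance of at least one p < 0.05 is 1 − 0.95^k:
- k = 22: 1 − 0.324 = 67.6%
- k = 18: 1 − 0.397 = 60.3%

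The expected number of false positives among 22 tests is 22 × 0.05 = 1.1, whatever the correlation.

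**4. Allowing for correlation.** The protocol gives no correlation between indices, so a range was simulated: 22 equally correlated indices, 4 × 4 repeated-measures ANOVA, 12 participants, no true effects, 3,000 runs per value. The Monte Carlo standard error is at most √(0.25/3000) = 0.9 percentage points. The adjustment for sex and energy expenditure was not modelled.

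| Chance of at least one significant result | r = 0 | 0.3 | 0.5 | 0.7 | 0.9 |
|---|---|---|---|---|---|
| Interaction | 68% | 57% | 47% | 34% | 18% |
| Interaction or intervention main effect | 90% | 82% | 71% | 55% | 31% |
| Class versus class, session means, Bonferroni over 6 pairs | 41% | 36% | 30% | 22% | 11% |
| Class versus class at 10, 20 and 30 min separately, Bonferroni over 6 pairs at each time | 74% | 71% | 61% | 48% | 28% |

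The two class-versus-class rows do not require a significant F-test first. With 22 participants (1,500 runs) the interaction figures are 67% at r = 0 and 48% at r = 0.5, so recruiting the larger number does not reduce this error.

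**The case against.** Five points can be made against this.

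- **Independence does not hold.** By the protocol's own formulas, ESP is SV times Ea, Ea is built from R, C and Zc, CO comes from SV and HR, LF/HF comes from LF and HF, and the elastic modulus and β share the same pressures and diameters. This stands. The 68% is the independence figure, not an estimate for this trial, and 22 is not a firm floor. A narrow reading of the Purpose (HF, three PWVs, elastic modulus, β, AIx) leaves 7 indices, for which 1 − 0.95^7 = 30%.
- **A significant F-test is not a difference between classes.** A reader might infer that a chance difference between fitness classes is more likely than not. The documents do not support that. The F-tests include Control, and for class pairs on session means after Bonferroni the risk is 11% to 41%. It passes one half only if pairs are tested separately at each recovery time and the correlation is moderate or low. The protocol does not say which post-hoc layout applies.
- **No true differences is an unlikely state.** The section Descriptive Elements of the Project itself says that a single bout of exercise changes stiffness and autonomic function, so with a seated control many interactions may be real. This stands as a limit on the percentages, which are a benchmark. It does not tell the reader which significant indices to believe.
- **This is a small acute physiology crossover without an explicit confirmatory claim, and an SAP may exist.** Detail on secondary outcomes can be left to an SAP. The primary outcome cannot, because the sample size depends on it, and this protocol already fixes the tests, the threshold and the scope of Bonferroni.
- **Sizing is a weak reason to promote aortic PWV.** The Participants section says "Twelve apparently healthy adults aged between 21 to 34 years will be included in this study", against 22 required. Under the formula in step 1, power at 12 is 47.6%. The Purpose also lists parasympathetic reactivation first. Both are fair, and both need a decision by the sponsor, but neither supports leaving every index with equal standing.

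**Conclusion.** The point holds. The protocol names no primary outcome, sizes the study on aortic PWV alone, and tests about 18 to 22 indices at 0.05 each with no control across them. With 22 indices and no true differences, the chance of at least one significant interaction runs from about 68% (independence) through 47% (r = 0.5) to 18% (r = 0.9). These figures rest on an assumed equal correlation between indices and one interaction test per index. Counting intervention main effects as well raises them. The exact risk cannot be known from the protocol, but it exceeds 5% throughout the range examined. The defect lies in the missing hierarchy, so it does not depend on any one of these percentages.

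**What to change.** In Statistical Analysis and Data Monitorization, state that the single primary test is the intervention × time comparison for carotid-femoral (aortic) PWV, two-sided at 0.05, which agrees with the basis of the sample-size statement. Keep Bonferroni for the pairwise follow-up within that index, since the interaction alone does not separate the classes from one another. Label all other indices, including the parasympathetic ones in the Purpose, secondary or exploratory, and report them as estimates with 95% confidence intervals and no confirmatory claim. This holds the confirmatory error at 5%.

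The alternative of Bonferroni over all 22 indices (0.05/22 = 0.0023 each; 1 − (1 − 0.0023)^22 = 4.9% under independence) would also control the error, but would set a much stricter threshold in a small study.

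The cost is protocol wording and the loss of confirmatory claims on the other indices; no measurement is dropped. Separately, the 12 participants in the Participants section and the 22 in the power statement must be reconciled before any power is claimed for the primary test.
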